#### Invitation

The caregivers/parents of the eligible patients will be verbally invited during their hospital admission. The participant information sheet (PIS) will be explained to them in the language they understand.

#### Eligibility

Participants will be assessed based on the eligibility criteria enumerated above.

#### Enrolment

Eligible participants will be enrolled in the study after giving a written informed consent.

#### Informed consent

Parents and caregivers will give a written informed consent during enrolment. This will be signed by the principal investigator or co-investigator, the parent/caregiver and a witness. A copy of the informed consent will be retained by the parent, while a copy will be kept in the patient’s file.

### Sampling technique and assignment of interventions: allocation

An allocation sequence for the 2 arms will be generated for eligible patients using simple randomization from GraphPad Prism version 9. In the selected hospitals, patients with cerebral malaria, confirmed by a blood film malaria test (microscopy) but with a negative cerebrospinal fluid analysis result whose parents/caregivers give informed consent, will be assigned to one of the 2 arms based on the assignment sequence.

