## Trial design {8}

This will be a triple blinded, parallel randomized controlled trial consisting of one treatment (experimental arm: intravenous artesunate + quinine) and one control arm (intravenous artesunate). Patient allocation will be in the ratio of 1:1. The assignment of patients into the study arms will be randomized.

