### Study setting {9}

This study is a multi-centre RCT involving 4 tertiary hospitals (one private and three public) located in three of the six geopolitical regions in Nigeria [16, 17]. The selected tertiary hospital includes University College Hospital, Ibadan; Bowen University Teaching Hospital, Ogbomoso; the Federal Medical Centre Katsina, Katsina State; and the University of Maiduguri Teaching Hospital, Maiduguri.

All the facilities have the human capacity to manage critically ill children. Other details are given: administrative details (the ‘Administrative information’ section) and trial site locations (Fig. 2).

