### Sample size {14}

The sample size for this study was calculated using the G*Power calculator, based on the reported outcomes of cerebral malaria with quinine monotherapy (23.0%) and a dual quinine and artesunate combination therapy (12.5%) [10, 18–20]. Going for a difference of 23.0 to 12.5%, a sample size of 470 participants is required accounting for a 10% attrition rate at 80% power of a 2-sided alpha level of significance of 0.05. Based on 1:1 allocation, the treatment arm will have 235 participants and the same number for the control arm. The details of the selected studies for the sample size calculation are shown in a supplementary document as a table.

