### Statistical methods for primary and secondary outcomes {20a}

Data from this study will be analysed using the GraphPad Prism 9 (GraphPad Software, [name]). The appropriate descriptive statistics will be used to present the socio-demographic characteristics of study participants. The comparison of categorical outcomes between the arms will be analysed using the chi-squared or Fisher’s exact tests, as appropriate, and presented as risk differences, risk ratios, and 95% confidence intervals. Kaplan-Meier analysis and Cox regression models will be used to compare the recovery of consciousness, defervescence, and survival.

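### No 0 h parasite count is scheduled to support a density-based clearance rate, and unstratified randomisation with unadjusted survival tests forgoes a modest gain in precision

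*Protocol article*

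**What the plan says.** **Parasite measurements.** The Specific objectives include a parasite clearance rate read by microscopy. The Secondary outcomes section lists parasite density, and presence or absence of asexual forms, at 12 h and 24 h. Neither is given a baseline value, although that section names a baseline for the haematological and inflammatory markers. The Participant timeline {13} agrees: the parasitaemia row is marked at 12 h and 24 h and blank at 0 h, while haematology, inflammatory markers and glucose are marked at 0 h. Entry requires demonstrable parasites (Eligibility criteria {10}) and a confirming blood film (allocation section). No count is mentioned.

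**Allocation.** "An allocation sequence for the 2 arms will be generated for eligible patients using simple randomization from GraphPad Prism version 9". No section names blocking or stratification. The setting is described thus: "This study is a multi-centre RCT involving 4 tertiary hospitals (one private and three public) located in three of the six geopolitical regions in Nigeria". The Sample size {14} section expects that "the treatment arm will have 235 participants and the same number for the control arm".

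**Analysis.** The primary outcome is survival at 48 h. Under Statistical methods {20a}, "The comparison of categorical outcomes between the arms will be analysed using the chi-squared" or Fisher's exact test. The same section adds Kaplan-Meier and Cox analyses for survival, recovery of consciousness and defervescence, without naming covariates.

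**The concern.** A clearance rate in the density sense needs a starting value. Rapid parasite clearance is also part of the stated rationale for adding quinine, so the outcome is not peripheral. If the count at entry is not recorded in the same way at all four hospitals, it may not be recoverable later.

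Site, age and coma score are known for every child before randomisation. The design does not use site when it allocates, and the tests for the binary primary outcome use none of the three. At stake is precision in the mortality comparison that could be had without recruiting more children.

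**Working it through.** **1. Parasite density: which quantities the schedule supports**

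- Proportion cleared by 12 h and by 24 h: computable, because every child is positive at entry and presence or absence is recorded at both times.
- Unadjusted comparison of density between arms at 12 h and 24 h: computable.
- Fall in density from the start of treatment, or later density adjusted for its starting value: not computable from the scheduled data, because there is no 0 h value.
- Slope from 12 h to 24 h only: available only for children still positive at 12 h. That group is defined after randomisation, so the slope is a poor substitute.

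**2. The planned sample size**

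Inputs from Sample size {14}: 23.0% versus 12.5% (taken as death proportions), two-sided alpha 0.05, 80% power, 10% attrition, 470 children.

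Formula per arm, with p̄ = (0.23 + 0.125)/2 = 0.1775:

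n = [1.960 √(2 p̄(1 − p̄)) + 0.842 √(p₁(1 − p₁) + p₂(1 − p₂))]² / (p₁ − p₂)²
= [1.960 × 0.5404 + 0.842 × 0.5352]² / 0.105² ≈ 2.279 / 0.011025 ≈ 207.

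With attrition, 207/0.90 = 230 per arm, or 460 in total. The stated 470 is close to this and slightly generous.

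Power of the unadjusted test is 84.8% at 235 per arm and 81.0% at 212 per arm (470 × 0.90 = 423 evaluable). Fisher's exact test gives 82.3% and 78.1%. The smallest expected cell is about 212 × 0.1775 = 38 deaths per arm, so chi-squared is the natural choice of the two.

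**3. What simple randomisation does to arm sizes**

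With 470 children and probability 0.5, the difference in arm sizes has standard deviation √470 = 21.7. The chance of exactly 235:235 is 3.7%, and of a difference of 20 or more 38%. The effect on power is negligible: after attrition it is 80.9% at an even split and 80.9% at 213:257.

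The protocol gives no site sizes, so these are assumed. The chance of a 40:60 or worse split in a given site is 3.4% with 118 children, 15.5% with 60 and 36% with 30. With four sites of 118, the chance that a given site differs by 20 or more is 8.0%. The chance that at least one does is 1 − (1 − 0.080)⁴ = 28%. At that threshold (69:49) the variance in the site rises by a factor of (118/4)/(69 × 49/118) = 29.5/28.65 = 1.03, which is small.

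**4. What adjustment could gain**

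The protocol gives no prognostic strength, so a range was simulated: 4,000 runs, 423 children, simple randomisation, marginal death rates 23.0% and 12.5%, and one standardised baseline index with log-odds ratio b per standard deviation. The unadjusted z-test was compared with a logistic model containing the index.

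| b (assumed) | Power unadjusted | Power adjusted | Gain (points) |
|---|---|---|---|
| 0 | 81.5% | 81.5% | 0 |
| 0.5 | 80.4% | 81.7% | 1 |
| 0.8 | 80.8% | 84.2% | 3 |
| 1.0 | 81.0% | 85.4% | 4 |
| 1.5 | 82.2% | 91.1% | 9 |

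Simulation error is about √(0.8 × 0.2/4000) = 0.6 points per entry. With no treatment effect, both tests rejected in 4.6% to 5.5% of runs.

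A model with several covariates is feasible: about 211.5 × (0.23 + 0.125) = 75 deaths are expected under the planning rates.

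**The case against.** Much of the opposing case stands.

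- **Bias.** A reader might infer that chance imbalance distorts the mortality result. It does not. Simple randomisation is valid, the confidence interval already allows for chance imbalance, and the simulated type I error stays near 5% without adjustment. Missing exactly 235 per arm has no consequence, since that figure is a planning target.
- **No correction at all.** A reader might infer that imbalance necessarily goes uncorrected. The protocol also plans Cox models for survival. These can carry covariates, and an analysis plan that is not shown could list them. What can be said is that the tests assigned to the binary primary outcome take none and that the article names no adjustment.
- **Missed power.** A reader might infer a shortfall against the planned 80%. With chi-squared there is none. The 1 to 9 points are an improvement not taken, and their size depends on the assumed b.
- **Unanswerable objective.** A reader might infer that the clearance objective cannot be met. Read as a proportion cleared, in the sense in which the same list uses survival rate, it can be. A blank 0 h cell is also not proof that nothing is recorded: the row for regained consciousness is blank at 0 h too, yet the coma score is needed for entry.

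What remains is narrower. A baseline is named for the other laboratory markers but not for parasite density. The allocation method is fixed as simple. Neither an unscheduled count nor the allocation can be put right by an analysis plan once children are enrolled.

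**Conclusion.** The point holds in limited form. As scheduled, the protocol supports the proportion cleared by 12 h and 24 h, but not a density-based clearance rate or a baseline-adjusted density comparison. This affects a secondary outcome. For the primary outcome, unstratified allocation and covariate-free tests are valid and adequate for the planned power, but less precise than the information available at entry would allow.

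The gain forgone is about 1 to 9 points of power for b between 0.5 and 1.5, and none if the baseline variables do not predict death. The site-split probabilities rest on assumed site sizes. These are inexpensive improvements that should be made, not corrections of an invalid design.

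**What to change.** 1. **Secondary outcomes and Participant timeline {13}:** add a quantified parasite count at 0 h, read from the diagnostic film. Compare log density at 12 h and 24 h between arms adjusted for log density at 0 h, and state how zero counts enter the log scale. Keep the proportion cleared as it is. Cost: one count on a film already made.
2. **Statistical methods {20a}:** make the primary 48 h survival analysis a logistic regression adjusted for site, age and baseline coma score, with the score entered within its own scale because older and younger children are scored differently. Report a standardised risk difference with its 95% confidence interval, and keep the unadjusted chi-squared test as a sensitivity analysis. Cost: a little more analysis, and a check that the chosen software produces the standardised estimate and its interval.
3. **Allocation section:** replace simple randomisation with permuted blocks of randomly varying size, stratified by site. Centres already call a central pharmacologist for each allocation, so only the list changes. Blocking makes allocations slightly more predictable; central holding, blinding and varying block sizes keep that small.

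The Trial status section reports that recruitment is not under way, so on that status all three can be made before the first child is randomised.

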### Sequence generation {16a}

Sequence generation and patient’s allocation to either an experimental arm of intravenous artesunate and quinine and a control arm of intravenous artesunate and intravenous 10% dextrose water by the centrally located clinical pharmacologist (unblinded) who has no link with the other research team.

### Concealment mechanism {16b}

Participants’ allocation to any of the treatment arms will be concealed from the investigators, the patients, and the statistician (triple blinding) in an opaque envelope. The clinical pharmacologist will deliver an allocated intervention consisting of a box with a unique identification number linked to the sequentially generated number. The box would contain the study drug, case record form, and all the disposable required for drug administration and blood sampling by the physician. The packaging for the drugs and the dextrose water shams will be similar for both the treatment arm and the control. Centres will call the central pharmacologist to get concealed numbers at the time of enrolling a patient. When a patient is enrolled, one of the sealed envelopes will be opened for the allocation.

### Implementation {16c}

A clinical pharmacologist will implement randomization and treatment allocation for the multisite study with the aid of interactive voice response system interventions.

### Assignment of interventions: blinding

#### Who will be blinded {17a}

The treatment will be triple blinded. The investigator/clinician, parents/caregivers, and the consultant paediatrician (outcome assessor) will not be aware (blinded) of the interventions.

#### Procedure for unblinding if needed {17b}

When there is a serious adverse event that is life-threatening or features of quinine toxicity, the clinical pharmacologist will be called to unblind the allocation since he is the only one who has access to the concealed allocation.

### Data collection and management

#### Plans for assessment and collection of outcomes {18a}

Prior to the commencement of the trial, a pilot study of 20 patients will be conducted at the University College Hospital Ibadan site only, where the steering committee members are alongside the focal leads from the other three collaborating centres in order to test the questionnaire and the protocol. Data from the pilot study will be entered into a Microsoft Excel spreadsheet uploaded into GraphPad Prism version 9 and checked for appropriateness, completeness, and adequacy. Observation from the dummy analysis will be used to improve the data entry and address other observed limitations.

A debriefing session will be held to review the research process and appropriate adjustments where needed to improve the quality of the instrument and enhance understanding of the protocol for a better outcome. Subsequently, the site principal investigators will step down such training to the collaborating centres.

#### Plans to promote participant retention and complete follow-up {18b}

The study participants will be contacted via their phone to remind them of the next visit to the neurologist. The transportation fare will be borne by the research sponsor to facilitate retention on follow-up.

#### Data management {19}

Data obtained from the study will be entered into a password protected and encrypted institutional REDCap database. Only specific individuals from the collaborating centres will be given access to the database. All data from all the centres will be de-identified and managed through secure code. The data assessor (statistician) will be blinded to the data until the final stage of analysis.

#### Confidentiality {27}

All information collected in this study will be given code numbers, and no name will be recorded. This cannot be linked to the patients, parents, or care providers in any way. Identifiers will not be used in any publication or reports from the study.

#### Plans for collection, laboratory evaluation, and storage of biological specimens for genetic or molecular analysis in this trial/future use {33}

This trial has no intention for a genetic study on the respondent.

### Statistical methods for primary and secondary outcomes {20a}

Data from this study will be analysed using the GraphPad Prism 9 (GraphPad Software, [name]). The appropriate descriptive statistics will be used to present the socio-demographic characteristics of study participants. The comparison of categorical outcomes between the arms will be analysed using the chi-squared or Fisher’s exact tests, as appropriate, and presented as risk differences, risk ratios, and 95% confidence intervals. Kaplan-Meier analysis and Cox regression models will be used to compare the recovery of consciousness, defervescence, and survival.

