### Outcomes {12}

#### The primary outcome

The primary outcome is survival measured at 48 h post-randomization.

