#### Secondary outcomes

Number of patients that regained full consciousness as measured by GCS/MGCS of > 11 for children > 5 years or Blantyre Coma Scale of > 3 in children < 5 years at 12 and 24 h post-randomization.Number of patients with asexual form of malaria parasite present or absent at 12 and 24 h post-randomization.Number of patients that achieved fever defervescence (attainment and sustenance of axillary temperature of < 37.5 °C) at 12 and 24 h post-randomization.Parasite density at 12 and 24 h post-randomization.Number of patients with neurologic deficits at the fourth week (day 29) post-intervention in each of the arms. Neurology deficit is defined as the presence of impaired cognitive, motor or cranial nerve palsy and or persistence of convulsions.Time to convert to a full dose of enteral artemisinin-based combination therapy.The side effect profile (adverse events and serious adverse events) of medication in each arm of study: (i) solicited side effects include hypoglycaemia, arrhythmia, thrombocytopenia, tinnitus and anaemia; (ii) unsolicited adverse events as reported by patients post-randomization; (iii) random plasma glucose will be measured 6 hourly until 48 h after parasite clearance. Hypoglycaemia will be corrected with 2-4 ml/kg of 10% D/W and maintenance with glucose infusion at 6–8 mg/kg/min until euglycaemic; (iv) electrocardiography will be recorded before the administration of anti-malaria and 4 h after an intervention. The QT and RR will be measured by software and checked manually. Bazett’s formula will be used to correct the QT interval (QTc = QT/RR**0.5). Prolonged QT interval managed as per hospital protocol; (v) haematocrit, serum ferritin, platelet count and erythrocyte sedimentation rate will be monitored at baseline and 24 h and 48 h post-randomization.Plasma levels of inflammatory markers including C reactive protein, procalcitonin, lactate dehydrogenase and interleukin 6 at baseline, 24 h, and 48 h. Inflammatory markers and cytokine are included to assess a possible ‘cytokine storm’ in the course of parasite clearance.

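### Recovery of consciousness, defervescence and day-29 deficits are compared with no account of death, which precludes them and is expected to differ by arm

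*Protocol article*

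**What the plan says.** Under Statistical methods for primary and secondary outcomes {20a}, the protocol article states that "Kaplan-Meier analysis and Cox regression models will be used to compare the recovery of consciousness, defervescence, and survival". The same section says "The comparison of categorical outcomes between the arms will be analysed using the chi-squared or Fisher’s exact tests", with risk differences, risk ratios and 95% confidence intervals. It names no denominator.

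Under Secondary outcomes, consciousness and fever appear as counts at 12 and 24 h: "Number of patients that regained full consciousness as measured by GCS/MGCS of > 11" (with a Blantyre threshold for younger children) and "Number of patients that achieved fever defervescence". Specific objectives, however, lists recovery of consciousness as a time. The late outcome is "Number of patients with neurologic deficits at the fourth week (day 29) post-intervention in each of the arms", and "Neurology deficit is defined as the presence of impaired cognitive, motor or cranial nerve palsy and or persistence of convulsions". All of these are findings in living children.

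"The primary outcome is survival measured at 48 h post-randomization". The sample size is "based on the reported outcomes of cerebral malaria with quinine monotherapy (23.0%) and a dual quinine and artesunate combination therapy (12.5"%).

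The section on non-adherence and missing data {20c} provides for a per-protocol analysis and a report of how many children have missing data. No section says how a child who dies before waking, before defervescence or before day 29 enters these comparisons.

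**The concern.** A child who dies in coma never wakes. That child's recovery time is not unknown in the way that a lost child's is. Censoring at death treats the child as someone who would have gone on to recover at the same rate as those still alive, so one minus Kaplan-Meier estimates recovery in a setting where nobody dies. Listing recovery and defervescence with survival in one sentence hides the fact that death is the event in one analysis and an obstacle in the other two.

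The trial is built on the hypothesis that deaths differ by arm, so the distortion would differ by arm too. A deficit at day 29 can be found only in a survivor, so a plain count falls as mortality rises. The secondary efficacy results could then blur, or appear to contradict, a true survival benefit.

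**Working it through.** **Inputs from the protocol article.** Rates of 23.0% and 12.5%, 235 children per arm, two-sided alpha 0.05, 80% power, 10% attrition (Sample size {14}). Survival horizon 48 h (The primary outcome). Counts at 12 and 24 h (Secondary outcomes).

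**Assumptions.** The two rates are read as mortality. Recovery rates, timing of deaths and deficit rates are not in the document and are varied below.

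**The plan's own figure.** The pooled two-proportion formula for 23.0% against 12.5% gives 207 per arm, 414 in total. 414/0.9 = 460, within about 2% of the stated 470, so these are the rates the plan was sized on. Expected deaths are 235 × 0.23 ≈ 54 and 235 × 0.125 ≈ 29.

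**1. Equal recovery hazards, deaths censored.** Let r be the recovery hazard and d the death hazard, both constant, with d set to give the stated mortality at 48 h. Kaplan-Meier reports 1 − exp(−48r) in both arms. The proportion who really recover is r/(r+d) × [1 − exp(−48(r+d))].

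| r per hour | 1 − KM, both arms | Recovered, 12.5% mortality | Recovered, 23% mortality | Hidden gap (points) |
|---|---|---|---|---|
| 0.01 | 38.1% | 35.3% | 32.8% | 2.5 |
| 0.02 | 61.7% | 56.5% | 52.0% | 4.6 |
| 0.03 | 76.3% | 69.2% | 63.0% | 6.2 |
| 0.04 | 85.3% | 76.8% | 69.3% | 7.5 |

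The curves coincide although fewer children wake in the arm with more deaths.

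**2. Equal true recovery.** Per 1000 children in each arm, 200 recover at 12 h and 300 at 24 h, so 50% recover in both.

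- All deaths within 24 h (120 before 12 h and 110 after, against 65 and 60): 1 − (680/880)(270/570) = 63.4%, against 1 − (735/935)(375/675) = 56.3%. The arm with more deaths looks 7 points better.
- Half the deaths within 24 h (60 and 55, against 32.5 and 30): 1 − (740/940)(385/685) = 55.8%, against 1 − (767.5/967.5)(437.5/737.5) = 52.9%. It looks about 3 points better.

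**3. The Cox hazard ratio.** Let R be the proportion recovered and D the proportion dead at 48 h. With constant hazards the cumulative recovery hazard is −ln(1 − R − D) × R/(R + D).

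- R = 60% in both arms: −ln(0.17) × 0.60/0.83 = 1.281 with 23% mortality and −ln(0.275) × 0.60/0.725 = 1.068 with 12.5%. The ratio is 1.20 in favour of the arm with more deaths.
- R = 48% with 23% mortality, against R = 50% with 12.5%: the ratio is 1.07, still in favour of the arm with more deaths.
- R = 55% against 60%: the ratio is 1.00, so a real 5-point deficit disappears.

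**4. Day-29 deficits.** With the same deficit rate q among survivors in both arms, expected counts are 235 × 0.77 × q and 235 × 0.875 × q. Their ratio is 0.77/0.875 = 0.88 whatever q is, so the arm with more deaths shows 12% fewer deficits. At q = 10% the counts are 18.1 and 20.6, while death or deficit is 0.23 + 0.077 = 30.7% against 0.125 + 0.0875 = 21.3%.

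Dividing by survivors does not cure this if the extra survivors are the sicker children. Suppose they carry a 30% to 40% deficit risk and the rest 10%. The rate among survivors is then (0.077 + 0.105 × 0.30)/0.875 = 12.4% to (0.077 + 0.105 × 0.40)/0.875 = 13.6% in the low-mortality arm, against 10% in the other. Death or deficit is 23.4% to 24.4% against 30.7%.

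**The case against.** **Censoring is not stated.** The article names Kaplan-Meier and Cox without saying that deaths are censored, and an analysis plan might keep dead children in the risk set to the end of the window. This stands as a limit: the figures in steps 1 to 3 hold under the usual default. But the article does fix the method, and that method gives a proportion recovered only if death is treated explicitly. A cause-specific hazard ratio is valid as a rate among children still alive. It cannot be read as benefit when mortality differs.

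**The arm with more deaths always gains.** A reader might infer this, and the documents do not support it. With equal recovery hazards that arm looks equal, not better. It looks better when deaths remove the children least likely to wake, which is plausible in cerebral malaria but not shown. The 7 points need every death to fall within 24 h.

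**The 12 and 24 h counts ignore death.** This is also too strong. Over all randomised children, a child who has died counts as not recovered and the comparison is sound. The denominator is not given, though, and the analysis is per protocol.

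**Deaths after 72 h are lost.** The timeline's survival row stops at 72 h, but its adverse-event row runs to day 29 and beyond, and fatal events are reported as serious adverse events. A recording route exists.

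**Only two recovery times can ever be observed.** The timeline schedules the assessment only at 12 and 24 h. But treatment and the switch to enteral therapy depend on regaining consciousness, so staff will know when it happens. The gap is that the time is not a scheduled item.

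**The deficit count is wrong and must go.** Read beside survival, it is a legitimate description of morbidity, and a composite alone would hide that signal.

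**The mortality rates are an inference.** The sample size section speaks of outcomes, and its 23.0% is for quinine monotherapy, not the artesunate control. This stands as a stated assumption. If mortality were equal in the two arms, the differential distortion would disappear.

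**Conclusion.** The point holds for secondary outcomes. The planned Kaplan-Meier and Cox comparisons of recovery and defervescence, and the day-29 deficit count, take no account of a death rate that the trial expects to differ by arm.

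If deaths are censored and mortality is 23% against 12.5%, a true gap of about 2.5 to 7.5 points in recovery at 48 h can be hidden, or a false advantage of about 3 to 7 points at 24 h can appear for the arm with more deaths. Which of these occurs depends on recovery rates and death timing that the document does not give. The 12% shortfall in deficit counts needs only the mortality figures and equal deficit rates among survivors.

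Survival at 48 h, the primary outcome, is not affected.

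**What to change.** In {20a}, analyse recovery of consciousness, defervescence and time to enteral artemisinin-based combination therapy by cumulative incidence with death as a competing event, using Gray's test or a Fine-Gray model. A cause-specific hazard ratio may be shown beside it. Compare the 12 and 24 h counts over all randomised children, with those who have died counted as not recovered.

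In the participant timeline and case record form, add the clock time at which consciousness is regained, so that the time-to-recovery objective has data behind it.

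Under Secondary outcomes, keep the deficit count and add death or neurologic deficit by day 29 over all randomised children, with vital status recorded at the day-29 contact.

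The cost is wording, one or two form fields and possibly software other than GraphPad Prism. No extra visit is needed and the sample size does not change.
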